## Background

With advances in cancer treatments and the increase in long-term survivors, concerns are shifting from survival to quality of life after cancer and long-term side effects of treatments [1, 2]. Treatments combining surgery, radiotherapy, and chemotherapy are likely to alter reproductive function and quality of life after cancer [3, 4]. Access to fertility preservation is an essential element of quality of life for patients and their families after their recovery [5]. It is therefore becoming an increasingly important part of cancer management.

In many countries, recommendations include informing patients of the risks of infertility associated with cancer treatment, and referring them as soon as possible after diagnosis to a specialized center for fertility preservation consultations [6–8]. In France, since 2004, there is a legal obligation to offer fertility preservation to any woman or man exposed to a treatment likely to impair their reproductive function [9]. In 2018, a study based on National French data estimated that between 17,200 (10,400 men and 6,800 women) and 40,000 (30,000 men and 10,000 women) patients of childbearing age were eligible for fertility preservation consultations and associated fertility treatments [10]. Focusing our attention on women, fertility preservation data provided by the French National Biomedicine Agency estimated that about 750 ovarian tissue self-preservations were carried out in 2013 [11], rising to 3,500 in 2018 [12]. These figures remain very far away from the expected number of individuals concerned, highlighting the need to drastically improve information and access to fertility preservation counselling.

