### Trial design

We will conduct a two-arm, multi-site, stepped-wedge cluster randomized trial in two participating French regions over a 30-months period (objective 2). Centers accredited to treat cancer will be grouped into 6 clusters to define the study sites depending on geographical position. The order in which these groups will have access to the intervention will be randomized. Depending on the stage at which a group is randomized, after a period of usual care of 7, 10, 13, 16, 19, or 22 months, the intervention will run for 22, 19, 16, 13, 10, or 7 months, respectively, in each group. We chose a stepped-wedge design to examine how the effect of the intervention evolves over time, to limit the risk of contamination within a site, and to ensure that the intervention is implemented in a way that maximizes adherence to optimal use, with 1-month training and transition period (see Fig. 2). Further, this type of trial ensures the access to the intervention for all participants. Eligible patients (*N*=750) seeing participating health professionals at these sites will be recruited.

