**Fig. 2 Fig2:**
[figure not shown]
Stepped-wedge cluster randomized trial plan

Data will be collected throughout the trial, which will allow us to compare the percentage of patients who have access to a fertility preservation consultation before and after the distribution of updated brochures and the awareness training of health professionals. This will allow us to assess the impact of these tools on the primary outcome measure.

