**Fig. 4 Fig4:**
[figure not shown]
Morville’s “honeycomb” framework

We will use Morville’s “honeycomb” framework as an analytical lens to examine the data collected in relation to our hypothesis. Observations and field notes from interviews and focus group transcriptions will also be included in the analysis. Initial descriptive codes will be generated based on the Morville frame domains. Inductive coding will also be used to capture other naturally emerging themes. Categorical codes that combine the deductive and inductive codes will be developed in a third round of coding. Dual independent coding of 20% of all transcriptions will be conducted.

#### Analyses corresponding to objective 2

In response to our overall aim, we will compare the rate of fertility preservation counselling between the usual care phase and the intervention phase. We will use linear regression models as appropriate for the primary outcome measure. Because each group is exposed to the intervention for a different length of time, the results will provide potentially valuable insights into how quickly the intervention affects the primary outcome. As we will be training several clinicians at each site, we will use a mixed-effects design in which the clinician is a random effect and the group is a fixed effect. This approach will allow to analyse pooled information from all six groups while exploiting repeated measures by clinicians in each group. Furthermore, differences between patients’ socioeconomic position will be explored. In the absence of socioeconomic data in medical files, the patient’s address will be used to assign the level of social deprivation in their area of residence, based on Townsend’s definition of deprivation as a state of social disadvantage relative to the population average [36]. We will therefore geocode the patients’ address to find the corresponding IRIS, i.e. the smallest area for which socio-economic data are available comprising nearly 2000 inhabitants. More specifically, we will use an ecological deprivation level indicator, a French version of the European Deprivation Index (EDI) [37] which has been used in many studies to characterize the socioeconomic context and approximate individual socioeconomic position, including in cancer patients [38–40].

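### The primary stepped-wedge model, as the article states it, names no calendar-time term, so any trend in consultation rates during the trial would enter the effect estimate

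*Protocol article*

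**What the plan says.** The Trial design section describes a "two-arm, multi-site, stepped-wedge cluster randomized trial in two participating French regions over a 30-months period". Clusters cross over in random order: "after a period of usual care of 7, 10, 13, 16, 19, or 22 months, the intervention will run for 22, 19, 16, 13, 10," with 7 months for the last cluster, and "with 1-month training and transition period".

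The primary analysis appears only under Analyses corresponding to objective 2. The contrast is phase against phase: "we will compare the rate of fertility preservation counselling between the usual care phase and the intervention phase". The model family is given as "We will use linear regression models as appropriate for the primary outcome measure". The terms named are a random and a fixed effect: "we will use a mixed-effects design in which the clinician is a random effect and the group is a fixed effect". The Trial design section puts the same comparison in before-and-after terms: "compare the percentage of patients who have access to a fertility preservation consultation before and after the distribution of updated brochures".

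No section names calendar time, period, step or secular trend as a model term. The remarks on how quickly the intervention acts, and on the effect changing over time, concern time since exposure. The yearly rates from health insurance data belong to a parallel feasibility study and do not adjust the trial comparison.

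**The concern.** All clusters start in usual care and end in the intervention, so intervention months are later months. With group as a fixed effect and nothing for calendar time, the phase coefficient is a weighted average of six within-group before-after differences. The random order of crossover then gives no protection against a background trend. That protection comes from comparing clusters that are in different phases at the same calendar time, and the model must contain time to use it.

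If consultation rates drift upwards for other reasons during the 30 months, the drift is credited to the brochures and training, and a positive result could not safely be attributed to them. A downward drift would hide a real effect in the same way.

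**Working it through.** **The plan's own figure.** Sample size and power calculation states a detectable effect of 5.5 points (80% power, alpha 5%, 23% baseline, 6 clusters of about 120). A two-proportion comparison of 720 to 750 women split equally gives 9.1 to 9.3 points two-sided and 8.1 to 8.2 one-sided. The 5.5 points are therefore not reproduced even without a time term. That is a separate matter, but it bears on the fix.

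**Distance between the phases.** Let c be the months of usual care (7, 10, 13, 16, 19, 22; Trial design).

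- Usual care covers months 1 to c, with mean (c + 1)/2.
- Month c + 1 is the transition.
- The intervention covers months c + 2 to 30, with mean (c + 32)/2. Its length is 29 - c, which matches the stated 22 down to 7.
- Difference: (c + 32)/2 - (c + 1)/2 = 31/2 = 15.5 months, whatever c is.

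**Bias.** A linear trend of b points per year adds b × 15.5/12 = 1.29b to the phase coefficient. The order of crossover does not matter, because the gap is the same in every cluster.

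**Standard error without a time term.** Assume even accrual of 750 women over 6 × 30 = 180 cluster-months, i.e. 4.17 per cluster-month; binomial variance 0.23 × 0.77 = 0.1771; no clinician variance. Each cluster contributes c(29 - c)/29: 5.31, 6.55, 7.17, 7.17, 6.55 and 5.31, in total 38.07. SE = √(0.1771/(4.17 × 38.07)) = 3.34 points. Two-sided detectable effect at 80% power: (1.96 + 0.84) × 3.34 = about 9.4 points.

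**Type I error.** P(reject) is approximately 1 - Φ(1.96 - bias/SE); the opposite tail is negligible. The trends are assumed.

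| Trend, points/year | Bias, points | Bias/SE | Two-sided type I error |
|---|---|---|---|
| 2 | 2.6 | 0.77 | about 12% |
| 3 | 3.9 | 1.16 | about 21% |
| 4 | 5.2 | 1.55 | about 34% |

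At an assumed rate of 25% instead of 23%, the last two become about 20% and 32%. A trend of 5.5/1.29 = 4.3 points per year would by itself produce the whole stated detectable effect.

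**With a time term** (least squares on the same monthly grid, group fixed, N = 750, 23%):

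| Time term | Bias per 1 point/year | SE, points | Detectable effect, points |
|---|---|---|---|
| None | 1.29 | 3.34 | 9.4 |
| Linear month | 0 | 5.97 | 16.7 |
| Step periods | 0.02 | 6.20 | 17.4 |
| Month as factor | 0 | 6.24 | 17.5 |

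With random instead of fixed cluster effects (Hussey-Hughes variance, 7 periods, about 18 women per cell, assumed intracluster correlation 0 to 0.2), the detectable effect is about 11.6 to 14.2 points.

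**The case against.** The strongest reply is that this is a condensed article. The text says linear models will be used as appropriate and gives no equation. The sentence on random and fixed effects explains how clustering is handled and does not even list phase. The full protocol or an analysis plan may contain a period term, and a phase-against-phase contrast is the usual stepped-wedge estimand, fully compatible with one. Part of this stands: a reader might infer that the model is completely specified and that time adjustment has been ruled out, and the text does not support that. What remains is that the article does not leave the model open. It states the contrast, names one random and one fixed effect, and elsewhere describes a before-and-after comparison. An analyst who followed that text would run the confounded model.

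A reader might also infer that the document proves a rising trend in this outcome, since it reports "about 750 ovarian tissue self-preservations were carried out in 2013 [11], rising to 3,500 in 2018". It does not. Those are national counts of procedures without a denominator, not limited to breast cancer, and they end five years before the trial was registered. The one regional consultation rate, 23%, is pooled over 2012 to 2017 and shows no trend. The counts indicate a plausible direction and nothing about size.

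Finally, adjustment is expensive in precision. That is true, but the smaller standard error of the unadjusted model is valid only if there is no trend.

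**Conclusion.** The point holds for the model as the article states it. Only the 15.5-month gap, and so the multiplier of 1.29 for a linear trend, follows from the documents alone. The spurious effects of 2.6, 3.9 and 5.2 points are conditional on assumed rises of 2, 3 and 4 points per year. The error rates of roughly 12%, 21% and 34% rest further on even accrual, a 23% rate and no clinician variance. With no trend there is no bias; with a falling trend the bias reverses. It would go too far to say that the estimate is certain to be inflated, or that a standard error of 6.0-6.2 points is the inherent precision of this design: that value applies to fixed group effects. Because the primary estimate and the value of the randomised order depend on it, the model statement should be corrected before analysis.

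**What to change.** State the primary model as consultation (yes/no) on phase, calendar period as a fixed effect and group, with clinician random. Calendar period can be the seven step periods bounded by the six crossover dates, or calendar month. Make the phase coefficient from this model the primary estimate and label the unadjusted before-after comparison descriptive. If the full protocol or analysis plan already has such a term, say so in the model statement.

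No new data are needed: dates of diagnosis and of chemotherapy start are already collected (Data collection). Calendar period should be defined by the same date that assigns a woman to a phase.

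The cost is precision. With fixed group effects the standard error rises from about 3.3 to about 6.0-6.2 points, and the two-sided detectable effect at 80% power from about 9.4 to about 17 points, or about 12-14 with random cluster effects. The 5.5 points in Sample size and power calculation must therefore be restated for the period-adjusted model, with the assumed intracluster correlation and the choice of fixed or random group effects given.

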In Europe, a Dutch retrospective study conducted at the Radboud University Medical Center found that only 9.8% of all eligible patients under the age of 40 and seen at a university hospital in 2011 were referred for fertility preservation counselling. In addition, this study found that referral to counselling was hampered by a lack of information about the services offered by fertility preservation centers, and by a lack of collaboration among healthcare providers [13]. In Denmark, a study conducted in 2023 among young women with cancer and informed of the risks to their fertility showed that their doctors’ choice of treatment was not in favour of preserving their fertility, as survival was more important [14]. In France, a lower rate of self-reported discussion of infertility risk (46%) was reported by the 102 of 1161 oncologists who responded to a national survey between 2012 and 2013. Moreover, only 22% of oncologists reported referring the patient to a fertility center before starting treatments [15]. More recently, the FEERIC study (FErtility, prEgnancy, contRaceptIon after breast Cancer in France) showed that around 46% of survey respondents were offered specialized oncofertility counselling [16].These results are all the more worrying considering that 80% of female respondents had a high level of education, with university degrees and therefore a high level of literacy.

French regional studies carried out in Occitanie (a region in the south-west France with a population of 6 million) have shown that only 23% of women under 40 treated with chemotherapy for breast cancer received an oncofertility consultation and 8.7% received fertility preservation between 2012 et 2017. Only 44% of oncologists were confident that ovarian stimulation treatment could be used, and 29% overestimated the time required for fertility preservation [17]. Information and access to an oncofertility consultation were influenced by the type of care structure, the woman’s age, her parity at the time of diagnosis, and the metastatic status of the cancer [18]. Furthermore, another regional study showed that if all women were informed of the risks of hypo fertility related to chemotherapy, then gamete preservation could be increased by 15.35% in women aged < 30 and 22.88% in women aged 30 to 35 [19].

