### Participants

All oncologists practicing in accredited cancer centers will be invited to participate in the stepped-wedge cluster randomized trial. The managers of the RCNs involved in the project will liaise with health professionals in those cancer centers. In both regions 60 cancer licensed centers will be involved in our trial, 44 in Occitanie and 16 in Pays de la Loire. These centers will be classified in 6 randomization groups (clusters), and each cluster will have access to implemented information tools and newly created training resources for practitioners at different times as shown in Fig. 1.

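### The primary model has no cluster-by-period term, so its standard error for the phase effect is too small if outcomes vary by cluster and period

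*Protocol article*

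**What the plan says.** The analysis model is in the protocol article under Analyses corresponding to objective 2. The model type is given as "We will use linear regression models as appropriate for the primary outcome measure". The correlation structure follows: "we will use a mixed-effects design in which the clinician is a random effect and the group is a fixed effect". The reason given is that several clinicians are trained at each site, and the next sentence describes the gain: "This approach will allow to analyse pooled information from all six groups while exploiting repeated measures by clinicians in each group". No cluster-by-period, centre or calendar-time term is named.

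The design is described elsewhere. Under Participants, "In both regions 60 cancer licensed centers will be involved in our trial", and "These centers will be classified in 6 randomization groups (clusters"). Under Trial design, clusters are formed by geographical position, their order is randomised, and each crosses over "after a period of usual care of 7, 10, 13, 16, 19, or 22 months", "with 1-month training and transition period". Under Sample size and power calculation, the total is 750 women with a control rate of 23%. No ICC or cluster autocorrelation is given anywhere.

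**The concern.** With group as a fixed effect, the phase effect is estimated by comparing later with earlier months inside each cluster. A random intercept for clinician and a fixed intercept for group both describe differences that stay constant over time, and these cancel in that comparison. A change that affects a whole cluster for some months does not cancel. Clusters are geographical and the outcome is a consultation recorded at the assisted reproduction centres, so a temporary change in local capacity or referral practice is a plausible example, although the article does not document one. Such a change affects all clinicians in the cluster together, so the clinician effects cannot represent it.

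The phase contrast comes from six crossovers, so few independent shifts are averaged. If the shifts exist and are not modelled, the confidence interval is too narrow and a null intervention is declared effective more often than the nominal 5%.

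**Working it through.** The plan gives no standard error for the primary analysis. Its only precision figure, a detectable effect of 5.5 points, implies an SE of 5.5 / (1.960 + 0.842) = 1.96 points. That is below even the SE with no clustering found in step 2. It is a separate matter and is not used here.

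**Inputs from the article.** 750 women over 30 months in 6 clusters is 750 / 180 = 4.167 women per cluster-month. Crossovers come after months 7, 10, 13, 16, 19 and 22, each followed by one transition month that is left out. This gives 7 periods (7, 3, 3, 3, 3, 3 and 8 months), 42 cells and 750 − 25 = 725 women. The outcome variance at 23% is σ² = 0.23 × 0.77 = 0.1771.

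**Assumption.** Cluster-by-period variance τ² = ICC × σ². ICC 0.01 gives an SD of √0.001771 = 4.2 points, and ICC 0.02 gives √0.003542 = 6.0 points. These equal a total ICC of 0.05 or 0.10 with cluster autocorrelation 0.8, since 0.05 × 0.2 = 0.01 and 0.10 × 0.2 = 0.02. Clinician effects are left out of the formulas and brought back in step 5.

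**Step 1, weights.** With group fixed and no period effects, the estimate is a weighted mean of the six within-cluster differences. Cluster weights are proportional to h = u·t / (u + t), with u usual-care and t intervention months: 5.310, 6.552, 7.172, 7.172, 6.552 and 5.310, with sum H = 38.07.

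**Step 2, model SE.** √[σ² / (4.167 × H)] = √(0.1771 / 158.6) = √0.001117 = 3.3 points.

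**Step 3, true SE.** Each cell has weight b = (h/H) × (its months / months of its phase in that cluster). The extra variance is τ²·Σb². For the cluster crossing at month 7, the usual-care cell contributes 1 and the intervention cells (2, 3, 3, 3, 3, 8 of 22 months) contribute 104/484 = 0.215. Multiplied by (5.310/38.07)² this gives 0.0236. The other five clusters give 0.0250, 0.0260, 0.0267, 0.0271 and 0.0232, so Σb² = 0.1517.

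- ICC 0.01: √(0.001117 + 0.001771 × 0.1517) = √0.001385 = 3.7 points
- ICC 0.02: √(0.001117 + 0.003542 × 0.1517) = √0.001654 = 4.1 points

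**Step 4, period effects added.** The same least-squares calculation with six period contrasts gives Σb² = 0.3381 and a model variance of 0.003842, so a model SE of 6.2 points.

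- ICC 0.01: √(0.003842 + 0.001771 × 0.3381) = √0.004440 = 6.7 points
- ICC 0.02: √(0.003842 + 0.003542 × 0.3381) = √0.005039 = 7.1 points

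Type I error is 2Φ(−1.96 / r), where r is true SE over model SE.

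| Model | ICC | r | Type I error |
|---|---|---|---|
| As written | 0.01 | 1.114 | 7.8% |
| As written | 0.02 | 1.217 | 10.7% |
| Period effects added | 0.01 | 1.075 | 6.8% |
| Period effects added | 0.02 | 1.145 | 8.7% |

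**Step 5, simulation with clinicians.** 2,000 null trials per scenario, with 60 centres, an assumed 2 clinicians per centre and an assumed clinician ICC of 0.05 (Monte Carlo error about 0.5 to 0.8 points):

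| Omitted component | As written | Period effects added |
|---|---|---|
| None | 4.0% | 6.2% |
| Cluster-by-period ICC 0.01 | 8.7% | 6.9% |
| Cluster-by-period ICC 0.02 | 10.2% | 8.7% |
| Cluster-by-period ICC 0.05 | 17.2% | 13.7% |
| Constant centre ICC 0.05 | 5.0% | 4.4% |
| Centre 0.03 plus centre-by-period 0.03 | 6.1% | 5.1% |

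In a further simulation (4,000 null trials per scenario, same two cluster-by-period SDs), an analysis of the 42 cells with cluster and period effects and a t reference on 42 − 13 = 29 df rejected in 4.4 to 5.0%.

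**The case against.** The strongest objection is that this is a condensed article, that models are to be used as appropriate, and that random-effects detail and small-sample corrections are commonly left to an analysis plan. This stands for the correction and the permutation test, whose absence is not a fault of the article. It does not stand for the correlation structure. The article names what is random and what is fixed and gives its reason, and an analyst who follows that has no cluster-by-period term.

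Four stronger readings are tempting, and the documents do not support them.

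- *The model ignores that six units were randomised.* Group is the randomised unit and is a fixed effect, so constant correlation within it is absorbed. Repeated women per clinician are modelled too.
- *Leaving out centre invalidates the interval.* The Background does say "Information and access to an oncofertility consultation were influenced by the type of care structure", but that reports predictors of access in an earlier regional study. Constant centre effects are largely carried by the clinician effects and cancel within centre. Omitting them left type I error at 4.4 to 5.0%.
- *The interval is certainly too narrow.* No ICC is given, and at zero cluster-by-period variance there is no material error. The risk runs one way only, because positive variance always makes the SE too small.
- *Type I error could be several times nominal.* With a cluster-by-period SD of 6 points and a trend of 3 points a year, the written model rejected in 25.6% of simulated null trials. Adding period effects brought this to 8.4%. Most of the excess therefore belongs to the missing calendar-time term, a separate issue.

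**Conclusion.** The point holds in conditional form. The stated model gives no protection against variation shared by a cluster in a period, and the phase effect is exposed to exactly that variation. For an assumed cluster-by-period ICC of 0.01 to 0.02, the written model understates the SE (3.3 points against 3.7 to 4.1) and type I error is about 8 to 11%. Period effects alone do not cure it: 6.2 points against 6.7 to 7.1, and about 7 to 9%. At ICC 0.05 the simulated error rates are 17.2% and 13.7%. These sizes rest on the assumed ICCs, an even inflow of patients and equal cluster sizes. The direction of the error does not depend on those assumptions.

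**What to change.** In the primary model, keep clinician random and group fixed, add a random intercept for cluster-by-period, and use a Kenward-Roger or Satterthwaite correction. Alternatively, analyse the 42 cluster-by-period proportions with cluster and period effects and a t reference on 29 df. Support either with a permutation test over the 6! = 720 cluster orders. A centre random intercept is optional.

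The cost is model wording and minor programming, with no change to design, recruitment or data collection. Over the assumed ICC range the interval becomes about 11 to 22% wider than the written model's if only the cluster-by-period term is added (r = 1.114 to 1.217). Against a model that already has period effects it is about 7 to 15% wider (r = 1.075 to 1.145). Adding period effects itself roughly doubles the SE (3.3 to 6.2 points), but that cost belongs to the separate calendar-time issue.
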